### Suicidal ideation and suicidal behavior

For the purpose of this study, suicide attempt is defined as any act of purposeful self-harm with expressed suicidal intent, that is, the wish to die, as reported by the patient at the assessment or by a family member consulted as a key informant (no discrepancy), or recorded during treatment, within the first year of follow-up. Suicidal ideation will be measured with the Sheehan Suicidality Tracking Scale (S-STS). The S-STS is an eight-item prospective rating scale that tracks treatment-emergent suicidal ideation and behaviors [54,55]. Each item in the S-STS is scored on a five-point Likert scale (0 = not at all, 1 = a little, 2 = moderately, 3 = very, and 4 = extremely). Data from the S-STS can be analyzed as individual item scores, a suicidal ideation subscale score (sum of scores from items 2, 3, and 4, plus score from item 5 if ≥ 1), a suicidal behavior subscale score (sum of scores from items 6, 7a, and 8, plus score from item 5 if > 1), and as a total score. A higher score on the S-STS and its subscales corresponds to greater risk of suicide.

### Aggressive behavior

Aggressive behavior will be monitored with the Modified Overt Aggression Scale (MOAS). The MOAS rates overt aggression displayed by the patient in the period preceding the assessment [56,57]. Ratings are provided for the most severe act in four categories: verbal aggression, aggression against objects, aggression against oneself, and aggression against other people. Aggressive acts are rated from 0 (no aggressive behavior) to 4, with increasing severity from 1 to 4; then, scores are multiplied by a factor specific for each category: 1 for verbal aggression, 2 for aggression against objects, 3 for aggression against oneself, and 4 for aggression against other people [58]. The total score varies from 0 (no aggression) to 40 (maximum grade of aggression). A higher score on the MOAS and its subscales corresponds to a higher occurrence of aggressive behaviors.

### Side effects

Side effects to drugs will be closely monitored and coded with the Dosage Record and Treatment Emergent Symptoms Scale (DOTES). The DOTES is a 30-item scale aimed at recording changes in the patient’s health status that can or could be attributed to the prescribed psychopharmacological treatment (described in [34]). The scale lists symptoms and pathological conditions affecting the patient’s body, with a judgment required on their presence and severity, and a separate assessment of the actual or potential links with the patient’s prescribed drugs. The presence and severity subscale includes 4 levels, from 1 (absent) to 4 (severe, resulting in drug suspension). The subscale on the actual or potential links with the patient’s prescribed drugs includes 5 levels, from 1 (symptom absent or no link), to 5 (certain link, as certified in the literature). A higher score on the DOTES corresponds to a higher occurrence and severity of side effects, which may or may not be related to the patient’s prescribed drugs on the basis of the rating of the subscale on the actual or potential links.

### Follow-up assessment

The FPP has a six-month duration, so patients will be assessed at entry (t0), at the end of the FPP (t1), at the six-month follow-up (t2), and at the twelve-month follow-up (t3), for secondary outcome measures. Adherence will be monitored at t0, t1, t2, and t3, via self-reports, interviews and measured blood levels of the primary prescribed drug.

### Sample size and power

Sample size for the identification of the expected difference in the primary outcome (adherence to pharmacotherapy) was based on known evidence: prevalence of non-adherence to pharmacotherapy in patients already in contact with a psychiatric service is around 40 to 50%, median = 47% [11,12]; effect size of psychosocial treatment on various outcomes, including relapse, readmission and adherence to pharmacotherapy is 0.48 of the standard deviation (SD), with 95% CI= 0.10 to 0.85 [16]. We expect that our intervention could produce a change in the prevalence of non-adherence to pharmacotherapy in the exposed group with an effect size of 0.45 SD [11,12]. After performing a test of difference between proportions we determined that a sample of 78 participants per group would be needed to achieve 80% power to detect a difference with h = 0.45 (medium effect size) in the measures of adherence to pharmacotherapy, at a two-sided significance level of 0.05 and allocation ratio of 1:1.

Cohen’s h effect size for the difference of proportions is calculated on the formula:

$$h=2^{*}\arcsin\;p1-2^{*}\arcsin\;p2$$

where p1 and p2 are the proportions of adherent patients in the exposed group 1 and the non-exposed group 2, respectively [59]. The Cohen’s h measures the same effect size interval as the Cohen’s d but is based on differences by proportion rather than by continuous variables [59].

Cohen’s h = 0.45 implies that at the estimated power (= 80%) we can observe a 25.5% rate of non-adherence to pharmacotherapy in the exposed group as opposed to a 47% rate in the unexposed group. In this case, risk reduction is 0.215, corresponding to a number needed to treat (NNT) = 5. Since we do not know the exact proportion of non-adherence, here are the different starting p1 and related maximum p2 detectable:

p1: 0.65 0.60 0.55 0.50 0.45 0.40 0.35 0.30 0.25

p2: 0.43 0.38 0.33 0.28 0.24 0.20 0.16 0.12 0.09

Since this a multisite study, the clusterized nature of the data has to be controlled since it has an impact on an unequal variance by center, which requires a correction of the sample according to the formula:

$$\mathrm{DE}=1+\left(m-1\right)\times r$$

where m is the original sample size per cluster (in our study, m = 7.8 + 7.8 = 15.6 about 16), r is a value summarizing the intra-cluster correlation coefficient (ICC), and DE (design effect) is the correction needed to maintain the same effect size in the expected change produced by the treatment [60]. In most studies, the ICC varies between 0.02 and 0.05. With ten enrolling units, precautionary ICC equals 0.05 and DE 1 + (16–1)*0.05 = 1.75. Therefore, by multiplying the initial sample size (n = 156) by DE, the final ICC-corrected sample size is 273, equal to 27.3 about 28 patients per cluster.

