### Assessment and outcome measures

Assessment is aimed at investigating the clinical and functional status of the patients and evaluating the main effects of treatment on the primary and secondary outcome measures (Table 3). The primary outcome is the patient’s adherence to pharmacotherapy, intended as the continuous use of the primary prescribed drug. Even if patients with psychosis are generally under poly-pharmacotherapy, only adherence to the most important drug (the one expected to produce the main therapeutic effect), as indicated by the enrolling unit, will be monitored during the study. Adherence will be checked by a triple method of assessment: patient’s self-report on the Medication Adherence Rating Scale (MARS), patient’s replies to the four-query interview of the Brief Adherence Rating Scale (BARS), and measurement of blood levels of the prescribed drug. Data will be analyzed using two indicators of adherence:

1. a dichotomic index, where non-adherence is the lack of adherence to the treatment in 30% or more of the monthly evaluation on the self-report or the interview (since replies on both measures might not coincide);

2. a continuous index based on the scale - self-report or interview - which could be the most reliable by comparison with the measurement of blood levels of the primary prescribed drug, to apply statistical analyses of covariance and verify the impact of confounding variables on the primary outcome.

**Table 3 T3:** Timing of assessments of endpoints for efficacy and safety

	**T0**	**T1**	**T2**	**T3**
Background information (age, sex, diagnosis, and so on)	X			
Clinical Global Impressions	X	X	X	X
Brief Psychiatric Rating Scale (BPRS)	X	X	X	X
Positive And Negative Syndrome Scale (PANSS)	X	X	X	X
Social Performance Scale	X	X	X	X
Health of the Nation Outcome Scales (HoNOS)	X	X	X	X
World Health Organization Quality Of Life (WHOQoL)	X	X	X	X
The Family Questionnaire	X	X	X	X
Medication Adherence Rating Scale	X	X	X	X
Brief Adherence Rating Scale	X	X	X	X
Dosage Record and Treatment Emergent Symptoms Scale (DOTES)	X	X	X	X
Sheenan-Suicidality Tracking Scale (S-STS)	X	X	X	X
Modified Overt Aggression Scale (MOAS) 1.0	X	X	X	X
Blood sample for assessing of the blood level of the prescribed drug	X	X	X	X
Assessment of blinding				X

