### Assessment tools

The MARS is a ten-item yes/no self-report instrument. Total scores vary from 0 (low likelihood of medication adherence) to 10 (high likelihood). From this scale, we used the five items specifically referring to the taking or not of the medication [31,32]. Therefore in our MARS version, total scores vary from 0 (low likelihood of medication adherence) to 5 (high likelihood).

The BARS is a brief, pencil-paper, clinician-administered adherence assessment instrument [33]. The BARS consists of four items: three questions and an overall visual analog rating scale to assess the percentage of doses taken by the patient in the past month (0% to 100%). The visual analog scale rating serves as a final adherence determination. The three questions inquire about patients’ knowledge of their own medication regimen and episodes of missed medication taking, and include: number of prescribed doses per day (question 1); number of days, over the past month, the patient did not take the prescribed doses (question 2); and number of days, over the past month, the patient took less than the prescribed doses (question 3). A higher score on the BARS corresponds to better adherence.

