### Data management and analysis

All analyses will be based, as far as possible, on the intention-to-treat principle. Differences in the primary outcome (adherence to pharmacotherapy) will be analyzed with a two-tail test for proportions with the Miettinen exact test [61]. A multiple logistic regression will be carried out to control for the confounding variables [62] using adherence (yes/no) as the outcome to verify the impact of the FPP on controlling the impact of the confounding variables (sex, age, severity of the disorder, cluster).

Survival analyses will be performed using the Kaplan-Meier method, followed by the log-rank test to define the terminal events at both the start of non-adherence and the first relapse or readmission episode [63]. Intention-to-treat will be applied considering the primary and secondary outcomes [64]. Multiple imputations will be applied to integrate missing data [65].

As far as validation of the self-report (MARS) and the interview (BARS) measure of adherence with respect to the blood levels of the main prescribed drug is concerned, Spearman’s rho will be used to compare blood levels of the main drug with the self-report or the interview; partial correlation will be used to ascertain the links between blood levels of the main drug with the self-report or the interview by taking into account the other measures (the interview or the self-report, respectively).

All analyses will be done with Excel (Microsoft Excel 2013 running on Windows 8) (Chicago, IL 60606, USA) or the Statistical Package for Social Science (SPSS) version 17 for Windows.

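### The sample size takes an expected effect of 0.45 SD as Cohen's h = 0.45; the two are not interchangeable, so the 25.5% target, NNT of 5 and 80% power at 78 per group do not follow from it

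*Protocol article*

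**What the plan says.** All the sizing steps are in the protocol article, section Sample size and power.

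- Literature effect: the benefit of psychosocial treatment over mixed outcomes, "including relapse, readmission and adherence to pharmacotherapy is 0.48 of the standard deviation (SD), with 95% CI= 0.10 to 0.85".
- Expected effect for this trial: a change in the prevalence of non-adherence "in the exposed group with an effect size of 0.45 SD".
- Sizing: "a sample of 78 participants per group would be needed to achieve 80% power to detect a difference with h = 0.45". The test behind this figure is set "at a two-sided significance level of 0.05 and allocation ratio of 1:1".
- Bridge between the two indices: "The Cohen’s h measures the same effect size interval as the Cohen’s d". The same sentence adds that h is built on proportions and d on continuous variables.
- Consequence: h = 0.45 is written out as 25.5% versus 47% non-adherence, a risk reduction of 0.215 and an NNT of 5. A table of other detectable pairs follows.
- Inflation: 156 is multiplied by a design effect of 1.75 to give 273. Elsewhere the protocol gives 340 enrolled and says that 20% drop-out was allowed for.

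Under Assessment and outcome measures, the primary yes/no index is "a dichotomic index, where non-adherence is the lack of adherence to the treatment in 30% or more of the monthly evaluation". Either MARS or BARS can trigger it. A second, continuous index is planned for analysis of covariance. Under Data management and analysis, differences in the primary outcome "will be analyzed with a two-tail test for proportions with the Miettinen exact test".

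**The concern.** An effect in SD units describes how far a distribution moves. Cohen's h describes the distance between two proportions after an arcsine transformation. Small, medium and large carry the same numerical benchmarks for both, but that does not make 0.45 of one equal to 0.45 of the other. For a normal score split into yes and no, h is at most about 0.8 times d.

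The 25.5% rate, the risk reduction and the NNT have no separate source; the section derives them from h = 0.45. If the evidence supports 0.45 SD, these figures are too favourable. The 80% power claim then applies to a larger effect than the one expected. This section is the protocol's only power justification for the primary outcome.

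**Working it through.** **Inputs, all from Sample size and power unless noted.** Two-sided alpha 0.05; 1:1 allocation; 78 per group; control non-adherence 47% (range 40-50%); expected effect 0.45 SD; literature effect 0.48 SD; design effect 1.75. Enrolment of 340 is from the Overview and 20% drop-out from Potential limitations.

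**Formula for h.** I use h = 2·asin(√p1) − 2·asin(√p2). The printed formula shows no square root, which may be a text-extraction loss. The plan's nine tabulated pairs match the square-root form (h = 0.44 to 0.46).

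**1. Reproducing the plan.**
- n = 2(1.960 + 0.842)² / 0.45² = 77.5, so 78 per group; power at 78 is 80.2%.
- h(0.47, 0.255) = 0.452. The two-proportion formula also gives 78 per group, with 80.4% power.
- Risk reduction 0.47 − 0.255 = 0.215; 1/0.215 = 4.7, so NNT 5.
- 156 × 1.75 = 273; 273/0.8 = 342 after rounding up, close to 340.

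The arithmetic from h = 0.45 onward is therefore right. A two-sample comparison of means with d = 0.45 also needs 78 per group, so the required n is the same whichever index is meant and does not reveal the substitution.

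**2. Converting 0.45 SD to proportions, normal score (my assumption).**
- p_exposed = Φ(Φ⁻¹(0.47) − 0.45) = 0.300.
- h(0.47, 0.300) = 0.352.
- Risk reduction 0.17; 1/0.17 = 5.9, so NNT 6.
- Power at 78 per group = Φ(0.352·√(78/2) − 1.960) = 59.5% (59.1% by the two-proportion formula).
- 80% power needs 127 per group before any design effect.

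**3. Sensitivity at 78 per group.**

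| Conversion | Control rate | Effect | Exposed rate | h | Power |
|---|---|---|---|---|---|
| Normal | 40% | 0.45 SD | 24.1% | 0.343 | 57% |
| Normal | 47% | 0.45 SD | 30.0% | 0.352 | 59-60% |
| Normal | 50% | 0.45 SD | 32.6% | 0.355 | 60% |
| Normal | 47% | 0.48 SD | 28.9% | 0.375 | 65% |
| Logistic | 47% | 0.45 SD | 28.2% | 0.392 | 68-69% |
| Logistic | 47% | 0.48 SD | 27.1% | 0.416 | 74% |

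The logistic rows use log odds ratio = d·π/√3. No row reaches 80%.

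**4. The shift that the stated target requires.**
- Normal: Φ⁻¹(0.47) − Φ⁻¹(0.255) = 0.58 SD.
- Logistic: [ln(0.47/0.53) − ln(0.255/0.745)]·√3/π = 0.952 × 0.551 = 0.53 SD.

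**5. Power at the planned size, 0.45 SD normal (47% versus 30.0%).** 340 × 0.8 = 272, or 136 per group.
- Without a design effect: Φ(0.352·√(136/2) − 1.960) = 83%.
- With 1.75: effective 136/1.75 = 78 per group, so 59%.
- With no loss (170 per group): 90% without the design effect, 69% with it.

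**The case against.** **The calculation is correct for the target it states.** The plan writes its target as 47% versus 25.5% and words the effect as a change in prevalence. For those rates, 78 per group does give 80%. This stands: the fault is the step from 0.45 SD to those rates, not what follows it.

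**The h/d sentence can be read as being about shared benchmarks.** It continues with a qualifier, and the section calls h = 0.45 a medium effect. That reading is fair, but shared labels would not justify carrying the number across, and the section gives no other ground for doing so.

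**The 60% figure depends on a model.** The literature effect pools outcomes such as relapse and readmission, and how it was derived cannot be seen here. This stands, which is why a range is given. Both conversions tried stay below 80% at 78 per group.

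**A reader might infer that the trial as planned has only 60% power.** The documents do not support that. The figure belongs to the base size, or to the planned size only if the 1.75 factor is accepted. The randomization section allocates individual patients 1:1 within each unit, stratified by location, so that inflation is doubtful for the treatment comparison.

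**A reader might also infer that the yes/no index throws away a graded scale and that BARS should become primary.** The interview's graded rating is described as decisive for that instrument: "The visual analog scale rating serves as a final adherence determination". But the yes/no index is a rule over monthly evaluations on two instruments, not a stated cut of one score. A continuous index is already planned, and the choice of scale is deliberately left to the comparison with blood levels. Naming BARS now would pre-empt that choice.

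**Conclusion.** The concern holds as a fault in the justification of the target effect. An effect of 0.45 SD does not equal h = 0.45. On a normal-score conversion at 47% control non-adherence it means about 30% in the exposed group, and the base size of 78 per group is about 20 percentage points short of the claimed 80% power. On a logistic conversion the shortfall is about 11 to 12 points.

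These figures assume that 0.45 SD is a shift of an underlying adherence score and that the yes/no index behaves like a cut of that score. The trial itself is probably not badly underpowered for 0.45 SD, since 136 per group without the design effect gives about 83%. But that margin comes from an inflation the plan introduced for another reason, not from the derivation it presents. The figures need correcting; the primary endpoint does not need to change.

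**What to change.** In Sample size and power, remove the h/d equivalence as the basis for the target, then do one of the following:

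1. Keep 0.45 SD. Name the conversion assumed and restate what follows from it: on a normal score about 47% versus 30%, h about 0.35, risk reduction about 0.17, NNT about 6, and about 60% power at 78 per group. Give the power at the planned 340 with 20% loss, with and without the design effect.
2. Keep 47% versus 25.5% as the target. State that at the base size the yes/no test is powered for a shift of about 0.53-0.58 SD, which is larger than the 0.45 SD expected and the 0.48 SD cited.

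Keep the yes/no index as primary. The continuous index already planned can also carry a supporting between-arm comparison; making BARS primary is optional.

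The cost is a revised paragraph and its figures, with no new data or patients. Under the first option the stated power at the base size becomes less favourable; under the second, the plan admits to needing a larger effect.

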### Randomization procedures and bias-minimization methods

All patients will be randomized in the exposed (FPP) or the unexposed (GT) group with a 1:1 allocation ratio in each unit, as each unit is expected to participate in the enrollment of both groups. Randomization will be carried out by the method of blocks of randomized permutations (to preserve balancing between the exposed and the non-exposed groups). Randomization will be stratified by location due to the multisite nature of the study. Correctness of the randomization procedure will be monitored at regular intervals.

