### Planned interventions

The FPP aims at improving communication and problem-solving abilities in patients and their families through sessions focused on: assessment of the individual’s and the family’s strengths, weaknesses, and goals; education about schizophrenia and treatment; communication skills training; problem-solving training; and training to cope with special problems [19]. Treatment sessions are provided on a weekly basis for six months (one and a half hours for each session). The first six sessions will be provided to each individual family with the participation of the patient and the caregivers, while the following sessions up to the 18th will be provided to clusters of families, according to a multi-family revised version of family psychoeducation [28,29].

The GT is a treatment providing general information on the disorders and with the same frequencies as the FPP (Table 2). The GT treatment sessions are also provided on a weekly basis for six months (one and a half hours for each session). Each GT session is structured in three steps: first, a short (20 minutes maximum) and hopefully informative introduction on selected topics concerning the main problems related to the disorder (see Table 2 for details); then family members are asked to discuss whether and how they faced the problem described, whether the solution was effective and why, and they are then are invited to imagine alternative solutions to the problem that differ from the solutions they adopted; finally, a ten-minute conclusion summarizes the main elements of the topic discussed during the meeting. This scheme is specifically effective in multi-family meetings, when different families are invited to discuss and compare the problems they faced and the solutions they adopted, and whether effective or not.

**Table 2 T2:** Timing and structure of the planned interventions: Falloon and co-workers’ Psychoeducation Program (FPP) and Generic Treatment (GT)

**Sequence**	**Month**	**FPP**	**GT**	**Type of meeting**
1 week	1	Introduction	Introduction on schizophrenia	Single family
2 week	1	Evaluation of individual family members	Meeting on delusions, hallucinations and apathy	Single family
3 week	1	Whole family evaluation	Meeting on depression, shame and risk of suicide	Single family
4 week	1	1. Informative meeting on schizophrenia	Meeting on drugs	Single family
5 week	2	2. Meeting on drugs	Meeting on aggressive behavior	Single family

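### The site-level design effect does not fit within-site randomisation, and its cluster size of 16 contradicts the 27 to 28 per site that it produces

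*Protocol article*

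**What the plan says.** In the protocol article, Sample size and power, the base calculation finds that "a sample of 78 participants per group would be needed to achieve 80% power to detect a difference with h = 0.45", "at a two-sided significance level of 0.05 and allocation ratio of 1:1". In rates, this means that "we can observe a 25.5% rate of non-adherence to pharmacotherapy in the exposed group as opposed to a 47% rate in the unexposed group".

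The same section then corrects for the multisite structure with DE = 1 + (m − 1) × r. It takes m as the original number per site with both arms added together (7.8 + 7.8 = 15.6, about 16). It gives an ICC range of 0.02 to 0.05 and chooses the upper end: "precautionary ICC equals 0.05 and DE 1 + (16–1)*0.05 = 1.75". The result is that "the final ICC-corrected sample size is 273, equal to 27.3 about 28 patients per cluster". Potential limitations adds that a 20% drop-out rate was included, and the enrolled number is 340.

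On allocation, Randomization procedures and bias-minimization methods states: "All patients will be randomized in the exposed (FPP) or the unexposed (GT) group with a 1:1 allocation ratio in each unit". Randomisation is also stratified by location.

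On delivery, Planned interventions gives the first six sessions to single families, "while the following sessions up to the 18th will be provided to clusters of families". Table 2 marks sessions 7 to 18 as multi-family in both arms. Recruitment and baseline procedures provides two therapists per unit for the FPP and GT together.

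**The concern.** The formula used is the inflation for trials in which all members of a cluster receive the same arm. Differences between clusters then add to the variance of the treatment contrast. Here each site contributes both arms in equal numbers, so a site with generally high or low adherence shifts both arms together.

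There is a second fault inside the formula. The number of sites is fixed at ten, so inflating the total also inflates the number per site. A design effect computed at 16 per site cannot belong to a trial that ends with 27 to 28 per site.

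What is at stake is how the result is read. The Discussion allows that GT may prove as effective as FPP and considers preferring GT in that case. A reader facing a null result will look to the stated power and detectable difference, and the derivation given supports neither at 273.

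**Working it through.** **Inputs (all from the protocol article).** Two-sided alpha 0.05, 80% power, h = 0.45, 47% vs 25.5% non-adherence, ten units, ICC 0.02 to 0.05 with 0.05 chosen, m = 16, N = 273 (Sample size and power); 20% drop-out (Potential limitations); 340 enrolled (Overview); 1:1 allocation within each unit (Randomization procedures).

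**Formulas.** n per arm = 2(1.96 + 0.8416)² / h². Power = Φ(h·√(n/2) − 1.96), where n is the effective number per arm, that is, the actual number divided by DE. Rates are converted on the arcsine-square-root scale, on which 47% vs 25.5% gives h = 0.452.

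**1. The protocol's own figures reproduce.**
- n per arm = 2(2.8016)² / 0.45² = 77.5, so 78; power at 78 is 80.2%.
- DE = 1 + 15 × 0.05 = 1.75; 156 × 1.75 = 273.
- 273 / 0.8 = 341.25, against 340 enrolled; 340 × 0.8 = 272 completers.

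**2. Design as randomised, no clustering within arm (DE = 1).**
- 273 analysed: 0.45 × √(136.5/2) − 1.96 = 1.76, power 96.1%.
- 272 analysed: power 96.0%. The h detectable at 80% is 2.8016 × √(2/136) = 0.340, that is, 47% vs about 30.5%.
- A simulation with ten sites of 27, individual randomisation within site and a site ICC of 0.05 on the logit scale gave power 96.2% and type I error 4.4%. Site-level variation alone cost nothing.

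**3. The protocol's premise (sites as whole clusters) with the cluster size it arrives at, m = 27.3.**

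| ICC | DE | Effective N | Power at 273 | N for 80% with ten sites |
|---|---|---|---|---|
| 0.05 | 1 + 26.3 × 0.05 = 2.315 | 118 | 68.6% | 674 |
| 0.02 | 1 + 26.3 × 0.02 = 1.526 | 179 | 85.3% | 222 |

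The last column solves N = 156 × [1 + (N/10 − 1) × ICC]. The value m = 16 would fit N = 273 only with 273/16, or about 17, sites.

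**4. Clustering within arm.** Assumption, not stated in the document: the two therapists per unit make 20 caseloads, each within one arm, so 272/20 = 13.6 completers each. The ICC range is the document's 0.02 to 0.05, which it gives for sites.

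| ICC | DE | Power at 272, h = 0.45 | h detectable at 80% | Rates |
|---|---|---|---|---|
| 0.02 | 1 + 12.6 × 0.02 = 1.252 | 91.3% | 0.380 | 47% vs 28.7% |
| 0.05 | 1 + 12.6 × 0.05 = 1.63 | 82.8% | 0.434 | 47% vs 26.3% |

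**The case against.** The strongest reply is that the sample size is about right, even if the reason given for it is wrong. Four parts of that case deserve an answer.

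- **The 80% is not printed beside 273.** This is correct. The article states 80% for 78 per group, and that statement is sound. It offers 273 as the number that preserves the calculation after correction, so 80% at 273 is implied. The point is about that implied figure.
- **The error is conservative.** This stands for the trial as randomised. The recruitment target and the type I error rate are not harmed.
- **The allowance of 1.75 is close to what within-arm clustering could need.** At ICC 0.05, the therapist-level assumption gives 1.63 and a detectable difference of 47% vs 26.3%, almost the protocol's 25.5%. This limits the consequence. It does not rescue the derivation, which names the site as the cluster and pools both arms.
- **Within-site randomisation cancels differences in level, not differences in treatment effect between sites.** This stands, and it is why the cancellation is described as large rather than complete. The Aims section stresses heterogeneous units, six of which have FPP experience. The document gives no figure for effect variation. As an assumption, treating sites as random with a between-site SD of 0.1, 0.2 or 0.3 in h, 272 completers give power of about 95%, 91% or 83%.

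Two stronger readings are tempting, and the document supports neither. A reader might infer that the trial really has 96% power and detects a clearly smaller difference than claimed. That needs no clustering within arm at all, which sits badly with shared multi-family groups and therapists. A reader might instead infer that the trial is underpowered at 69%. That figure treats sites as whole clusters, which is not how patients are allocated, and it becomes 85% at the document's lower ICC.

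**Conclusion.** The concern holds as an error in the sample-size justification. The site-level design effect does not apply to a trial in which "with a 1:1 allocation ratio in each unit, as each unit is expected to participate in the enrollment of both groups". On its own terms it also uses a cluster size that contradicts its result, which moves the implied 80% to about 69% at ICC 0.05 or about 85% at ICC 0.02.

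For the design actually described, the site inflation errs on the safe side. A defensible main figure is 83% to 91% power for 47% vs 25.5%. It rests on three assumptions: 272 completers, 20 single-arm caseloads of 13.6, and an ICC of 0.05 to 0.02 carried over from sites to therapists. The article does not say that each therapist delivers only one arm, nor how large the multi-family groups are, so the range is illustrative. The 96% is a ceiling.

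**What to change.** Keep 340 enrolled. In Sample size and power:

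1. Remove the site-level design effect and state that randomisation within site, stratified by location, handles differences in outcome level between sites.
2. Give the main power figure with a clustering allowance at therapist or multi-family-group level within arm, naming the assumed cluster size and ICC. On the assumptions above, this is DE 1.25 to 1.63, power about 91% to 83% for 47% vs 25.5%, and 80% power at 47% vs about 28.7% to 26.3%.
3. State whether each therapist delivers one arm or both, and the intended size of the multi-family groups, and recompute if they differ from the assumption.
4. If the unclustered figure is quoted (about 96%, or 80% power at 47% vs about 30.5%), label it an upper bound.
5. Bring the list of detectable proportions in the same section into line with the restated figures.

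The cost is a rewritten paragraph. Recruitment, randomisation and assessments do not change.
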